## Abstract

**Background:**

Aged long-term care receivers are affected by various adverse skin conditions like pressure ulcers, incontinence-associated dermatitis, dryness, intertrigo, and many more. Prevention of these skin problems and the provision of general hygiene and skin care activities are key areas of nursing practice. Numerous condition-specific guidelines are available and are implemented separately. On the other hand, there is huge overlap in terms of etiology, pathogenesis, and prevention of the skin conditions mentioned above. This leads to fragmented practice neglecting shared etiologies and prevention and treatment principles.

**Methods:**

The overall aims of this trial are to test the feasibility and to estimate possible effects of the implementation of a comprehensive skin care and prevention strategy targeting main nursing-relevant skin problems at the same time. A two-arm cluster-randomized controlled trial will be performed in 20 nursing homes randomly selected from the population of nursing homes of the state of Berlin, comparing skin care according to the skin care and prevention strategy with standard skin care.

**Discussion:**

It is expected that the implementation of this evidence-based skin care and prevention strategy will reduce the incidence of pressure ulcers, incontinence dermatitis, and other skin problems frequently related to care dependency. This trial will benefit individual patients and aged nursing home residents in general given the high prevalence and incidence of the addressed skin conditions. Findings of this exploratory trial may lay the foundation for a change in the development and evaluation of clinical standards and practices in general as it moves the perspective from individual conditions to a more comprehensive view on overlapping or coexisting health problems, in this case common skin conditions, in old-age long-term care receivers.

**Trial registration:**

The study is registered at the German Clinical Trials Register https://www.drks.de/drks_web/navigate.do?navigationId=trial.HTML&TRIAL_ID=DRKS00015680 (Deutsches Register Klinischer Studien, or DRKS; registration number: DRKS00015680, date of registration: January 29, 2019) and ClincialTrials.gov (registration number: NCT03824886, date of registration: January 31, 2019).

## Background

The substantial impact of age-related skin conditions, especially in old age, was recently emphasized in the latest World Health Organization (WHO) World Report on Ageing and Health [1]. The most common skin conditions in aged and care-dependent patients with a prevalence up to 99.1% in the long-term care setting are dry and vulnerable skin (including pruritus) and fungal infections with prevalences ranging from 14.3% to 64% [2, 3]. Aged and care-dependent patients are at high risk for developing pressure ulcers (PUs), skin tears (STs), intertrigo, and incontinence-associated dermatitis (IAD) [3, 4]. These are distinct clinical diagnoses, and condition-specific clinical guidelines and best practice recommendations are available [5–8]. On the other hand, these adverse skin conditions show many similarities in terms of etiology (e.g., skin fragility, immobility, and care dependency), prevention, and treatment [9].

For decades, preventive strategies implemented in clinical practice have addressed these particular skin conditions and risks separately. For example, a PU prevention policy exists in nearly every health-care institution today. Evidence-based strategies to prevent IAD, STs, or xerosis cutis are also increasingly developed. Based on local priorities and perceived needs, these recommendations are (partly) implemented or not. However, all of these distinct approaches have the same aim: to enhance and maintain skin integrity in aged and care-dependent people. Thus, proposed interventions have a lot in common: avoidance of skin-stressing insults (e.g., mechanical loading and safe handling) [7, 8], provision of skin protection and care (e.g., using protecting skin care products) [5, 7], moisturization of dry and cracked skin [6], and minimization of prolonged and repeated exposures to irritation (e.g., urine, stool, and surfactants from cleansing products) [5, 6].

Despite these shared commonalities, no overall evidence-based practice guidance exists for daily skin care in care-dependent elderly people. Facilities are challenged to implement fragmented, condition-specific guidelines, neglecting shared etiologies and prevention and treatment principles. Information overload and multiple and complex rules on the same topic have been shown to be important barriers to the implementation of evidence-based practice [10].

Skin care in general plays a fundamental role in daily nursing practice. However, the goals of providing skin care interventions do not always seem to be explicit [11], leading to a huge unexplained variability of skin care activities in daily practice [12, 13]. Research evidence suggests that current skin care is not always beneficial [14] and there seem to be misconceptions about the actual mode of action of skin care interventions [11].

Recently, an evidence-based skin care and prevention strategy was developed. The skin care strategy guides nurses through the care process starting from assessment to the allocation of targeted skin area interventions, taking into account available evidence, best practice, and guideline recommendations [15]. Implementation of the newly developed evidence-based skin health-promoting strategy will improve nurses’ knowledge, skills, and confidence in a core area of nursing practice. Additionally, it is assumed that the implementation of the skin care and prevention strategy will lead to an improvement of skin conditions, skin health, quality of life (QoL), and safety of elderly nursing home residents. However, the feasibility of implementation of this skin care and prevention strategy and its potential to influence assumed patient and intermediate outcomes have to be demonstrated before its clinical effectiveness can be examined on a larger scale.

## Objective

The overall aim of this trial is to implement a comprehensive and evidence-based skin care and prevention package that addresses common and largely avoidable adverse skin conditions in long-term care at the same time. The trial will answer the following research questions:Does the implementation of a skin care and prevention strategy reduce the incidence of PUs, IAD, intertrigo, and STs and the severity of dry skin in the intervention compared with the control group?How do different skin care regimens influence important skin barrier characteristics such as skin surface pH, stratum corneum hydration (SCH), and transepidermal water loss (TEWL)?Does the implementation of the skin care and prevention strategy reduce itch and pain and improve QoL?What are the effect sizes and intra-class correlation coefficients (ICCs) of the outcomes mentioned above?Is the implementation of a standardized skin care and prevention strategy feasible? What are relevant context factors?

## Methods, design, and analysis

### Design and setting

This exploratory study is a cluster-randomized pragmatic investigator-blinded parallel-group trial. The study will be conducted in a random sample of 20 out of 288 institutional long-term care facilities of the federal state of Berlin, Germany. Inclusion started April 2019 and the last nursing home resident will complete the study  March 2021.

### Nursing homes and participants

#### Eligibility criteria

The inclusion criteria at the institutional level are that (1) participating nursing homes must express a clear commitment to implement the skin care and prevention strategy if assigned to the intervention group, (2) participating nursing homes must have a valid PU prevention standard/algorithm in place, (3) only nursing homes providing written commitment to adherence to the trial procedures regardless of the outcome of randomization will be included, and (4) nursing homes have to have a minimum bed size of *n* = 70.

The inclusion criteria at the resident level are (1) living in the nursing home at the time of data collection, (2) age of at least 65 years, (3) “care degree 2 or higher” according to the German code book (Sozialgesetzbuch, or SGB) XI, and (4) written informed consent (from the resident or a legal representative). Residents at the end of life or with any dermatological condition or skin infestation requiring dermatological treatment or with known intolerance to any possible irritating product ingredients (e.g., urea or lactate buffer) or known hypersensitivity to any product ingredients (e.g., sorbid acid or cetylstearyl alcohol) will not be considered eligible.

### Interventions at the nursing home level

PU and IAD prevention and basic hygiene and skin care interventions are routinely delivered in German nursing homes. Therefore, nursing homes conducting PU prevention or other protective skin care activities (or both) according to “usual practice” will serve as the control group.

In the interventional nursing homes, a newly developed skin care and prevention strategy will be implemented on top on the existing care standards [15]. The skin care and prevention strategy will be delivered by nurses and consists of following components. Based on a comprehensive assessment, skin care will be provided. Condition-specific strategies for cleansing and the use of leave-on products will be given, including guidance on frequency of conduct/application and required product characteristics. For example, xerotic skin areas (e.g., extremities and feet) will be cleansed once daily or less often in the case of severe dryness, and lipophilic leave-on products, including humectants, will be applied at least twice daily or more often if needed. Personal care products will be used as long as they meet required product characteristics. If products are not available, a basic lipophilic emulsion (Lipophile Harnstoff Creme 5, Neues Rezeptur Formularium (NRF) 11.129) [16] will be delivered. Skin areas exposed to urine or feces (or both) will be cleansed after each incontinence episode by using mucosa-friendly mild cleansers, and a skin protection product that may include various product types (e.g., polymers) will be applied. If no products are available, a basic skin protectant (Weiche Zinkpaste DAB, NRF 11.21) [16] will be delivered and applied. Personal preferences of the residents will be taken into account during clinical decision making. The skin care and prevention strategy contains clear guidance when to involve medical experts. The components of this strategy will be adapted to local requirements as necessary.

This skin care and prevention strategy will be implemented by a combination of multiple strategies based on the normalization process theory [17], a socio-psychological middle-range theory which has been proven to be an effective framework for guideline implementation in nursing practice [18]. In addition, existing research evidence on the most relevant implementation barriers and facilitators [19–21] will be taken into account. Also, attention will be given to the four-phase model proposed by the German Network for Quality Improvement for implementing the National Expert Standards [22] because it is particularly relevant to the German nursing context.

### Strategies to improve adherence to intervention protocol

All implementation steps are designed to maximize adoption. Throughout the trial, continual communication with nursing home managers in either study group will be held to prevent early loss of clusters. Study visits to the nursing home wards conducted for data collection will maintain awareness and communication between caregivers and the study team. Because nursing home residents live in the institutions, there is a low risk that they will not be available at study visits. Before any inclusions, kick - off meetings will be held in the participating nursing homes. Study background and procedures are explained and the importance of following the study protocol is emphasized. A key project leader and additionally a “skin care team” per participating nursing home will be nominated and caregivers will be trained. The “skin care team” ideally will consist of three or four persons (e.g., quality manager, residential sector manager, and wound manager). The study team will support this team during the whole study (e.g., the study team will set goals with the project team onsite the nursing homes and will offer help at any time if problems arise) and evaluate the implementation process. Additionally, posters and flyers will be created and placed in the nursing homes for caregiver, residents, their relatives and legal representatives.

### Participant timeline

In total, four study visits are planned. After inclusion, residents will be followed up for 24 ± 1 weeks. Written informed consent will be obtained from the residents themselves or their legal representatives prior to study participation. All participating nursing home residents undergo a comprehensive demographic, nursing, medical, and dermatological examination. A detailed planned study schedule is shown in Fig. 1.

**Fig. 1 Fig1:**
[figure not shown]
Study schedule

### Outcomes and measurements

Owing to the exploratory and pragmatic nature of this trial, a broad range of outcomes will be measured. The main clinical outcomes are PU, IAD, intertrigo, and ST incidence and skin dryness per skin area. Fig. 2 shows the time points of measurement. All outcomes will be measured at baseline (week 0) and after 3 months (week 12 ± 1) and after 6 months (week 24 ± 1).

**Fig. 2 Fig2:**
[figure not shown]
Timeline of screening and study visits

#### Dermatological examination

PU incidence and location will be classified in accordance with the National Pressure Ulcer Advisory Panel/European Pressure Ulcer Advisory Panel (2014) [23]. The IAD incidence will be classified in accordance with GLOBIAD (Ghent Global IAD Categorisation tool) [24], and coded according ICD 11 (EK02.22) and the distinction between intact and eroded skin will be classified in accordance with the *Proceedings of the Global IAD Expert Panel* [5]. Intertrigo incidence and location will be classified in accordance with ICD 11 (EK02.2), and the ST incidence and location will be classified in accordance with the International Skin Tear Advisory Panel [25].

Dry skin per skin area will be classified in accordance with the overall dry skin (ODS) score [26, 27]. The ODS score is a clinical assessment of the presence and severity of skin dryness using a five-point scale. A score of 0 indicates no skin dryness whereas a score of 4 indicates advanced skin roughness, large scales, inflammation, and cracks [26].

#### Skin physiology measurements

In addition, skin function will be assessed by measuring SCH, TEWL, and skin surface pH, which are established parameters to characterize the skin barrier function and which have been used successfully in a similar trial in this setting [28].

SCH will be measured by using the Corneometer CM 825 (Courage + Khazaka, Cologne, Germany). This measurement is based on the differences of the dielectric constant of water and other substances. With this device, only the moisture content in the stratum corneum is measured [29]. The arbitrary units range from 0 to 120, and higher readings indicate higher SCH.

TEWL will be measured with the Tewameter TM 300 (Courage + Khazaka). The probe captures the constant permeation of water through the stratum corneum in grams per hour per square meter [30]. The measuring probe contains a pair of sensors that are located at different distances from the skin surface to determine temperature and relative humidity above the skin surface. The humidity gradient between both sensors is used for calculating the TEWL. Higher values indicate a higher TEWL. Skin surface pH will be measured with the Skin-pH-Meter^®^ PH 905 (Courage + Khazaka), a planar glass electrode. pH is a measure of acidity and alkalinity of a solution and it indicates the concentration of the hydrogen ions in an aqueous solution [31]. Reference values of human skin have been reported to range from 4 to 6 [32, 33].

The skin surface temperature of the skin areas will be recorded as well. It will be measured with the Skin-Thermometer ST 500 (Courage + Khazaka) in degrees Celsius.

#### Resident-reported outcome measures

QoL in residents without cognitive impairment will be assessed with the WHO - Five Well-being Index [34] and QUALIDEM [35] for residents with dementia. The German version of the WHO - Five Well-Being Index questionnaire published by the WHO in 1998 will be used. Scores range from 5 (all the time) to 0 (never) for a total of five items. Simple questions will be asked regarding well-being in the previous two weeks (e.g., “In the last two weeks … I was happy” or “… I was relaxed”). The sum scores range from 0 (indicating the lowest well-being) to 25 (indicating the highest well-being). A cutoff score of not more or equal than 13 is recommended.

The QUALIDEM assessment is a dementia-specific QoL instrument that is carried out by the nursing staff and that allows a proxy-based QoL rating in all stages of dementia. The German version of the QUALIDEM (version 2.0) published in 2015 will be used to assess the QoL of the resident of the previous seven days [35]. If the resident is affected by a mild to severe dementia, the 37-item assessment will be used. For residents with very severe dementia the 18-item instrument will be used. To assess whether the resident is affected by mild to severe dementia or very severe dementia, the global deterioration scale (GDS) will be used [36]. GDS scores from 2 to 6 indicate a mild to severe dementia, and the 37-item assessment of the QUALIDEM tool will be used. A GDS score of 7 indicates very severe dementia, and the 18-item QUALIDEM tool will be used.

Itch will be assessed with the 5-D Itch scale [37]. The score of the 5-D Itch scale ranges from 5 (no pruritus) to 25 (most severe pruritus) and contains five items measuring pruritus over the previous two weeks. Pain will be assessed with a numeric rating scale by residents without cognitive impairments and with a verbal rating scale by residents with cognitive impairments [38].

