#### Baseline assessment and covariates

Demographic variables (age, sex, care level, and highest educational level), main medical diseases, and medications will be obtained from medical records by trained study assistants. Data regarding skin self-care ability, incontinence and type will be obtained from the medical records or, if possible, via interview of the nursing home residents or the caregivers.

Functional assessments using the Braden scale and Barthel - Index will be conducted. The Braden scale is a six-item pressure ulcer risk assessment score with scores ranging from 6 (high-pressure ulcer risk) to 23 (no-pressure ulcer risk). The Barthel - Index measures physical function related to the daily activities using 10 items (e.g., washing and toilet use, eating and mobility or incontinence). Scores range from 0 (very dependent) to 100 (not dependent) [39].

All residents will be interviewed regarding their skin care habits. Data will be documented in structured source documents by trained study assistants. Variables for assessing skin care routine will be (1) washing habits, (2) showering habits, (3) bathing habits, (4) moisturizing habits of the face and body, (5) hair care, and (6) shaving habits. For all variables, the frequency, skin areas, used skin care products, and the residents’ ability to apply skin care by themselves will be documented. In case of cognitive impairment of the resident, the respective nurse will be asked or the information will be obtained from the medical records.

The residents or their caregivers will be asked regarding the date of the last visit by physician/specialty in week 0. If possible, the following information will obtained from the medical records:Is there a documentation of pressure ulcer risk in place?Are skin assessment results documented?If applicable, the type of pressure ulcer preventive mattress or seating cushion;The repositioning interval if bedfast;Seating hours if not able to stand up independently;Off-loading of heels if exposed to high risk of pressure ulcer;Skin care interventions provided (cleansing and leave-on products);Use of incontinence products and types;Incontinence skin care products.

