### Sample size calculation

Because the trial is exploratory in nature, a primary outcome is not defined. The sample size is determined such that the power of statistical tests is sufficiently high for each of several binary and continuous outcomes under realistic assumptions. According to the federal state government, there are 288 nursing homes in Berlin. According to the latest statistics (2015), the total number of nursing home residents in Berlin is 28,299. Given a mean of 100 residents per institution and a participation rate of 25%, the expected total number of residents is 25 per participating institution (500 in total). Taking into account a drop - out rate of 8%, each participating nursing home contributes about 23 residents to the trial. If m = 10 nursing homes are included in each study arm and given an ICC of ρ = 0.02 [41] and an incidence for the skin conditions of around p_C_ = 50% per annum (p.a.) (29.3% in 6 months) in the control group, the two-sided Z-test for difference in proportions at a level of α = 0.05 has a power of more than 80% if in the experimental group skin condition worsens in less than p_E_ = 29.8% p.a. (16.2% in 6 months). The power calculation for the clustered binary outcome was carried out using the method described in Ahn et al. [42]. For metrical outcomes such as the ODS score, the two-sided t-test can detect a minimal effect size (Cohen’s d) of d = 0.33 with a power of 80% at a significance level of α = 0.05. Again, an ICC of ρ = 0.02 is assumed. Therefore, the detectable effect sizes are relatively small for all outcomes. Since the effects of the experimental skin care regimen are expected to be larger, the study is not underpowered for each variable.

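### Pain and quality of life are split across different scales by cognitive status, so neither has one metric for the single effect size and ICC sought, and the claim of small detectable effects for all outcomes does not cover them

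*Protocol article*

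**What the plan says.** All references are to the protocol article.

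- **Pain** (Resident-reported outcome measures): "Pain will be assessed with a numeric rating scale by residents without cognitive impairments and with a verbal rating scale by residents with cognitive impairments". No conversion between the two scales is given.
- **QoL** (same section): "QoL in residents without cognitive impairment will be assessed with the WHO - Five Well-being Index [34] and QUALIDEM [35] for residents with dementia". The WHO-5 is a self-report over the previous two weeks, scored 0 to 25. QUALIDEM covers the previous seven days and is "carried out by the nursing staff and that allows a proxy-based QoL rating in all stages of dementia". It is split again by the Global Deterioration Scale (GDS): scores 2 to 6 receive 37 items, and for the rest "A GDS score of 7 indicates very severe dementia, and the 18-item QUALIDEM tool will be used".
- **Itch** (same section): "Itch will be assessed with the 5-D Itch scale". This is one scale, with no split.
- **Research question 3** (Objective): "Does the implementation of the skin care and prevention strategy reduce itch and pain and improve QoL". Research question 4 then asks for effect sizes and ICCs of the outcomes listed before it.
- **Power** (Sample size calculation): with 10 homes per arm, about 23 residents per home after drop-out and an ICC of 0.02, a two-sided 5% t-test has 80% power at d = 0.33. This is introduced for metrical outcomes, with the dry skin score as the example. The section continues "Therefore, the detectable effect sizes are relatively small for all outcomes" and concludes that power is adequate for every variable.

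**The concern.** The trial's declared purpose is to supply effect sizes and ICCs for planning a confirmatory trial. An effect size and an ICC belong to a particular measurement. A numeric and a verbal pain rating are not in the same units. The QoL instruments differ in units, and the WHO-5 also differs from QUALIDEM in rater (resident or nurse) and recall period (two weeks or seven days). Research questions 3 and 4 treat pain and QoL as one outcome each, but the data will hold two pain measures in two sets of residents, and up to three QoL measures in three sets.

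Two things are at stake. First, the confirmatory trial may be sized on pain and QoL estimates that come from only part of each home, or from a mixture of scales. Second, a reader of the sample size section would believe that pain and QoL share the sensitivity computed for an outcome measured in everyone. For pain, the gap arises at data collection: if the common question is never asked, no analysis plan can restore it.

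**Working it through.** **Inputs from the sample size section.** k = 10 homes per arm, m = 23 residents per home, ICC = 0.02, two-sided α = 0.05, power 80%.

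**Assumed input.** The share s of residents per home who use a given scale. The article gives no share with cognitive impairment, so 70%, 50% and 30% are shown, taken as equal in every home. With two pain scales, a 70% share on one means 30% on the other.

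**Formulas.**
- Design effect = 1 + (m − 1) × 0.02.
- Effective number per arm = 10m / design effect.
- Standard error of the standardised difference = √(2 / effective number).
- Test on 2 × 10 − 2 = 18 degrees of freedom, critical t = 2.101. Under the non-central t distribution, 80% power needs a non-centrality of 2.963, so detectable d = 2.963 × standard error.

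**The plan's own figure.** With m = 23, the design effect is 1 + 22 × 0.02 = 1.44, the effective number is 230 / 1.44 = 159.7 per arm and the standard error is √(2 / 159.7) = 0.1119. Detectable d = 2.963 × 0.1119 = 0.332. The stated 0.33 reproduces, so there is no arithmetic error.

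**The same calculation for one scale analysed alone**, with m = 23 × s:

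| Share on the scale (assumed) | Residents per home | Design effect | Effective number per arm | Standard error | Detectable d at 80% power | Power at d = 0.33 |
|---|---|---|---|---|---|---|
| 100% | 23.0 | 1.440 | 159.7 | 0.112 | 0.33 | 80% |
| 70% | 16.1 | 1.302 | 123.7 | 0.127 | 0.38 | 69% |
| 50% | 11.5 | 1.210 | 95.0 | 0.145 | 0.43 | 58% |
| 30% | 6.9 | 1.118 | 61.7 | 0.180 | 0.53 | 41% |

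**Sensitivity to the method.** A normal approximation in place of the t distribution gives power at d = 0.33 of 84% for the full sample and 74%, 62% and 45% for the three shares. The levels are higher and the pattern is the same. The t version is preferred because it is the one that reproduces the stated 0.33.

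**Reading across.** For any share below 100%, a scale analysed alone has a larger detectable effect than the one stated. QoL can be divided three ways, so at least one of its instruments would then be used by a third of residents or fewer.

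**The case against.** The best case for the plan has four parts.

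1. **Matching the instrument to cognitive ability is legitimate.** This stands. QUALIDEM is described as specific to dementia, with item sets by severity. The point is not that instruments differ, but that pain has no measure taken in everyone and that the power statement ignores the split.
2. **The loss of power is not inevitable.** Scores could be standardised within instrument and combined into one stratified effect using all 23 residents per home, and how strata are combined is ordinary content for an analysis plan that is not shown. This stands in part, and it is why the figures above are conditional on separate analysis. But standardising does not turn a resident's two-week self-report and a nurse's seven-day rating into one measurement, and it cannot supply a pain answer that was never collected.
3. **The power calculation is tied to metrical outcomes such as the dry skin score.** That is true of the calculation. The sentences after it extend it to all outcomes and every variable, and those sentences need limiting.
4. **The trial is exploratory**, has no primary outcome, and does not list pain or QoL among its main clinical outcomes. This limits the importance. It does not remove the point, because estimating effect sizes and ICCs is what the trial is for.

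A reader might go further in three ways that the article does not support.

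- *Research question 3 as a whole lacks a common scale.* It does not: itch has a single scale.
- *Impaired residents have no route to an itch score.* The article names no proxy for itch, although for skin care habits it says "In case of cognitive impairment of the resident, the respective nurse will be asked or the information will be obtained from the medical records". Silence in a condensed article is not an exclusion, and the full protocol may provide a route.
- *Residents whose cognition declines change instrument and are lost selectively from an analysis of change.* The article does not say that the instrument is chosen afresh at each visit; fixing it at baseline is compatible with the text. Nor does it state an analysis of change from baseline.

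**Conclusion.** The point holds for pain and QoL and for the reach of the power statement, and no further. As written, neither outcome has a common metric for the single effect size and ICC that research questions 3 and 4 seek. The stated d = 0.33 is correct for an outcome measured on one scale in all 23 residents per home. For a pain or QoL scale analysed on its own, the detectable effect is about 0.38 to 0.53 over assumed shares of 70% down to 30%, and power at d = 0.33 is about 69% down to 41%.

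These sizes rest on the assumed shares, the same share in every home, the plan's ICC of 0.02 applying within each subgroup, and separate analysis by scale. The direction does not depend on the particular share, but it does depend on separate analysis. The importance is moderate: the change is worth making before pain data are collected and does not threaten the main clinical outcomes.

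**What to change.** 1. **Pain.** Ask the verbal rating scale of every resident at weeks 0, 12 and 24 and name it as the common pain outcome. Keep the numeric scale as an addition for residents without cognitive impairment. Cost: one extra question per visit for those residents, and a coarser scale for the common outcome. The change works only prospectively; visits completed before it would lack the common answer for unimpaired residents.
2. **Power statement.** In the sample size section, limit d = 0.33 and the conclusion of adequate power to outcomes measured on one scale in all residents. Cost: wording only.
3. **QoL.** In the same place, say that QoL effects and ICCs will be estimated by instrument, with lower precision than for the other outcomes. Cost: wording only. This does not create a common QoL metric; it states plainly what the chosen instruments can deliver.
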